### Time points

The study included 5 follow-up visits in total: a baseline visit to sign the consent and to record the baseline information, 2 visits during treatment interval to record subjective vestibular questionnaires (DHI, VAS-V, and VAS-T) and hearing outcomes (PTA) and to monitor treatment safety outcomes, and 2 follow-up visits at 4 weeks and 8 weeks to assess hearing and vestibular functions and monitor safety outcomes. To optimize examination resources and reduce burden of examiners, among all five vestibular function tests (SOT, caloric test, vHIT, cVEMP, and oVEMP), only those with previous abnormal results will be repeated at follow-up visits.

The study flow diagram is shown in Fig. 1, and the SPIRIT figure of enrolment, interventions, and assessments is presented in Table 3.

**Fig. 1 Fig1:**
[figure not shown]
Study flow diagram (OP oral prednisone, ITM intratympanic methylprednisolone, DHI dizziness handicap inventory, VAS-V&T visual analogue scale for vertigo and tinnitus, PTA pure tone audiometry, SOT sensory organization test, VNG videonystagmography, vHIT video head impulse test, VEMP vestibular evoked myogenic potentials)

**Table 3 Tab3:**
[figure not shown]
The SPIRIT figure of enrolment, interventions, and assessments

*VNG* videonystagmography which includes the caloric test, *MRI-IAC* magnetic resonance of the internal auditory canal

*A follow-up test is only repeated when the previous test results in abnormal findings

### Adverse events

Any untoward medical occurrences with unfavorable symptoms in the participants are defined as adverse events (AEs). AE is not necessarily to have a causal relationship with the treatment. If the AEs are life-threatening, result in death, persistent, and significant disability or incapacity, or make the participants’ hospitalization, we define them as serious adverse events (SAEs). The investigators will routinely ask the patients if there have been any unexpected symptoms. Study-related and non-study-related AEs will be recorded in the patient’s clinical history by doctors in clinics and then reported to a trial investigator ([name]). Participants experiencing AEs will be followed up until the end of the events or the end of the trial. Any SAEs during this trial will be reported to the trial steering committee (TSC) and Adverse Drug Reaction Administration (ADRA) of the Eye & ENT Hospital of Fudan University within 48 h at learning of the event.

We list some possible study-related AEs here:
Short-term systemic use of glucocorticoids related SAEs: fracture, sepsis, and venous thromboembolism [29];Short-term systemic use of glucocorticoids related AEs: blood glucose problem, appetite change, sleep change, weight change; andIntratympanic injection-related AEs: ear pain, ear infection, tympanic membrane perforation, and worse vertigo after injection.

### Participant withdrawal

The participants will be informed of the right to withdraw from the study at any time after consent. The enrolled participants who are found ineligible later, lost to follow-up, or withdraw consent for any reason will be regarded as withdrawal. As for those who decided not to receive the protocol intervention, we will ask them if they would like to continue with the follow-up visits and if they agreed, their results will be regarded as variation other than withdrawals in ITT analysis.

We provide an online Wechat and telephone contacts to all the participants for timely communication and health education, which will promote the participants’ retention and adherence to the intervention protocols. Furthermore, we optimized the follow-up process by setting a specialty clinic for SSNHL, minimizing the waiting time, and waiving extra examination and treatment fees.

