### Recruitments and randomization

Patients who visit doctors from the outpatients and suspected of ISSNHL with vestibular dysfunction will be screened for eligibility. Eligible patients who consent to participate will receive either oral prednisone or intratympanic methylprednisolone randomly in a 1:1 allocation. The randomization sequence will be generated [contact], an internet website (https://www.random.org) producing true random sequence according to atmosphere noise. The concealed randomization sequence file will be constructed and kept in sequentially numbered, sealed, opaque envelopes by a staff member ([name]) in the Eye and ENT Hospital of Fudan University outside the study team. All the potential participants will be evaluated in strict chronological order of visiting time. When a patient is officially enrolled and numbered, the staff member will be contacted by telephone and open the corresponding envelope to find the randomized treatment for this patient. Assessors in examination rooms and statistician analysts are not allowed to receive any information of the group allocation. The information of participants will be referred using research code among investigators, and their personal information (like name and contacts) will be kept confidential before, during, and after the trial.

Following randomization, baseline information of the participants in demographic and clinical characteristics will be collected, such as age, gender, nationality, occupation, date of onset, predisposition, initial symptoms, time of diagnosis, any treatments before enrolments, body mass index (BMI), and comorbidities. The objective vestibular function evaluated by SOT, videonystagmography (VNG), vHIT, cVEMP, and oVEMP and the hearing outcome assessed by PTA will be performed at baseline and at 4 and 8 weeks after randomization, while the subjective vestibular dysfunction feelings reflexed by dizziness handicap inventory (DHI) and visual analogue scale for vertigo (VAS-V) and the tinnitus condition assessed by VAS in tinnitus (VAS-T, visual analogue scale for tinnitus) will be performed at baseline and at 1, 2, 4, and 8 weeks after randomization. Caloric test is routinely included in VNG. Acoustic impedance and magnetic resonance imaging of the internal auditory canal (MRI-IAC) will be performed only once at the baseline examination to exclude the potential misdiagnosed SSNHL.

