#### Primary outcomes

To evaluate the recovery of vestibular function, we set the recovery rates of the whole battery of vestibular function tests (SOT/caloric test/vHIT/VEMPs) as the primary outcome, which is the proportion of patients whose abnormal results of vestibular function tests at baseline recover to normal at 4-/8-week follow-up:
$$ \mathrm{recover}\mathrm{y}\ \mathrm{rate}=\frac{\begin{array}{c}\mathrm{number}\ \mathrm{of}\ \mathrm{patients}\ \mathrm{recover}\ \mathrm{from}\ \mathrm{abnormal}\ \mathrm{result}\ \mathrm{at}\ \mathrm{baseline}\\ {}\ \mathrm{to}\ \mathrm{normal}\ \mathrm{at}\ 4-/8-\mathrm{week}\ \mathrm{follow}-\mathrm{up}\end{array}}{\mathrm{number}\ \mathrm{of}\ \mathrm{all}\ \mathrm{enrolment}\ \mathrm{participants}}\times 100\%. $$

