### Blinding

We decide not to set blindness of the interventions to patients and doctors, because that setting blindness to patients and doctors will need placebo injections to some of the participants, which may bring unnecessary pain and tympanic membrane perforation risk to the patients. The specialists in test rooms and statistical analysts will be kept blinded during the trial until the statistical analyses are done.

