An ITT analysis and a per-protocol analysis will be both performed at each outcome. For the missing data in ITT analyses, if there is any, multiple imputation methods will be used. Up-to-date versions of SPSS (SPSS, Chicago, IL, USA) will be used to conduct analyses. A statistician from the Medical College of Fudan University will perform the analyses. Not until the statistician complete the analysis, will he be unblinded to the group allocations and the study hypotheses. All data sent to the analyst will be anonymized, and the study groups will be coded as groups A and B.

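### Randomised participants later found ineligible are classed as withdrawals, so an unblinded post-randomisation decision can cost outcome data and possibly ITT membership

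*Protocol article*

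**What the plan says.** Participant withdrawal puts three kinds of participant into one class: "The enrolled participants who are found ineligible later, lost to follow-up, or withdraw consent for any reason will be regarded as withdrawal". It then turns to participants who decide against the allocated treatment. They are asked whether they will keep attending, and if they agree, "their results will be regarded as variation other than withdrawals in ITT analysis". The section makes no such request of participants found ineligible.

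Four other parts of the protocol article bear on this:

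- **Blinding:** "We decide not to set blindness of the interventions to patients and doctors". Only the test-room specialists and the statistical analysts are blinded.
- **Participants:** the last exclusion criterion is open-ended and rests on the investigators' judgement.
- **Primary outcomes:** the denominator of the recovery rate is all enrolled participants.
- **Sample size and statistical methods:** "An ITT analysis and a per-protocol analysis will be both performed at each outcome", and "For the missing data in ITT analyses, if there is any, multiple imputation methods will be used".

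**The concern.** Loss to follow-up and withdrawn consent happen to a trial. A finding of ineligibility is made by the trial. Putting all three in one class means that a staff decision after allocation can end a participant's data collection. The contrast with treatment decliners, whose results are expressly kept, suggests that withdrawals are treated differently in the ITT analysis.

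The people placed to make that decision know the arm and may have seen the early course. If late ineligibility is found more readily in one arm, or in patients doing poorly, the comparison is no longer the randomised one. With 36 per arm, a handful of such decisions is enough to matter. The rule also fits badly with a primary denominator of all enrolled participants and with an ITT analysis that imputes missing results.

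**Working it through.** **The plan's own figure.** Inputs from Sample size and statistical methods: recovery 0.25 (oral) and 0.64 (intratympanic), two-sided 5%, Fisher's exact test, 80% power. Full enumeration of two independent binomials gives Fisher power of 0.794 at 29 per arm and 0.819 at 30. The stated 30 per arm reproduces, and the withdrawal rule does not alter it.

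**Reading the rules together, for a participant found ineligible after allocation.**

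1. Participant withdrawal: the participant is a withdrawal and is not in the group whose results are expressly kept in ITT.
2. Primary outcomes: the participant counts in the denominator, having been enrolled.
3. Sample size and statistical methods: a missing result in ITT is multiply imputed.

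Rules 2 and 3 can be combined: everyone enrolled stays in, and missing results are imputed. Rule 1 is the one that fits badly. It either leaves the participant out or needlessly turns an obtainable result into a missing one.

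**Can ineligibility come to light after allocation?** Recruitments and randomization says only eligible, consenting patients are randomised. The paragraph after the envelope procedure begins: "Following randomization, baseline information of the participants in demographic and clinical characteristics will be collected". It ends with acoustic impedance and MRI, which "will be performed only once at the baseline examination to exclude the potential misdiagnosed SSNHL". Interventions and comparisons starts treatment immediately after randomisation. Late discovery is therefore possible, and the withdrawal rule itself anticipates it. How often it would occur cannot be derived.

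**Size, as a hypothetical worst case.** Assumptions, not taken from the documents: true recovery equal in both arms at the midpoint of the planning values, (0.25 + 0.64)/2 = 0.445; 36 per arm; and k non-recoverers removed from one arm only. The apparent rate in that arm becomes 36 × 0.445/(36 − k) = 16.02/(36 − k). Type I error is the summed probability of all outcome pairs with p ≤ 0.05 after removal.

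| k removed | Apparent rate | Bias (points) | Chi-squared type I error | Fisher type I error |
|---|---|---|---|---|
| 0 | 0.445 | 0 | 4.6% | 2.5% |
| 3 | 16.02/33 = 0.485 | 4.0 | 7.4% | 4.7% |
| 4 | 16.02/32 = 0.501 | 5.6 | 7.9% | 5.9% |
| 5 | 16.02/31 = 0.517 | 7.2 | 10.7% | 7.6% |

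The chi-squared test (uncorrected here) is the one the plan names for comparing recovery rates; Fisher's test is the one it used for sample size.

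**Contrast.** If 4 participants leave one arm regardless of outcome (36 v 32), chi-squared type I error is 4.9%. The harm comes from selective removal, not from removal as such.

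**The case against.** The strongest reply is that nothing in the article removes anyone from ITT. The withdrawal section attaches a label, and the sentence on decliners can be read as naming two categories inside ITT: deviation with data, and withdrawal without. On that reading the all-enrolled denominator and multiple imputation already keep everyone. This stands in part. A reader might infer that three stated rules contradict each other, or that a missing result counts as a failure under the all-enrolled denominator. The article says neither. What survives is that late-ineligible participants are nowhere said to be kept or followed, while decliners are.

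A reader might also infer that late ineligibility is built into the design because the baseline work-up is described after allocation. The documents do not support that. Only eligible patients are randomised, inclusion requires an abnormal vestibular test, and the schedule in Table 3 is not shown, so the timing of MRI relative to allocation cannot be settled.

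A third tempting inference is a loss of power. If 20% dropout is counted as failure, 0.25 v 0.64 becomes 0.25 × 0.8 = 0.20 v 0.64 × 0.8 = 0.512. Fisher power at 36 per arm is then 73%, but under the planned chi-squared test it is 81.5%. If dropouts are removed instead, leaving 28 to 29 per arm, Fisher gives 78–79% and chi-squared 84.8–86.4%. Under the planned test, power stays above 80% either way, and the second case reflects the size of the dropout allowance, not the withdrawal rule.

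Finally, an article may leave the detail of analysis sets to the full protocol or SAP. That would answer a complaint about silence. Here the article states a rule, and the rule itself needs changing.

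**Conclusion.** The point holds as a matter of what the text permits. The article classes a staff decision of ineligibility with loss to follow-up, sets those participants apart from the ones whose results are expressly kept in ITT, and does so in a trial where doctors know the arm and one exclusion is discretionary. Outcome data can be lost this way, and ITT membership is left in doubt. The article does not say that withdrawals are deleted from ITT, and it does not name who judges ineligibility, so biased exclusion is neither prescribed nor shown.

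The tabulated bias of 4 to 7 points, and the type I error of 7.4–10.7% (Fisher 4.7–7.6%), rest on assumed counts, removal of non-recoverers only, from one arm only, and equal true recovery of 0.445. They show how sensitive a trial of 36 per arm would be; they do not predict its error rate. The change should be made because it protects the randomised comparison at little cost.

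**What to change.** In Participant withdrawal, remove late-discovered ineligibility from the withdrawal class. State that every randomised participant, including any later found ineligible, stays in the ITT set in the assigned arm and is invited to the 4- and 8-week assessments unless consent is withdrawn. State that missing results are multiply imputed, with all enrolled participants as the denominator, so that the withdrawal section, the primary outcome and the missing-data rule agree. Allow exclusion for ineligibility only from the per-protocol set, on facts that existed before randomisation, judged by someone blind to arm, and report the numbers by arm.

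The cost is protocol wording, a few extra follow-up visits, and slight dilution of the treatment contrast from including some ineligible patients. The planned sample size does not change on this account.

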### Blinding

We decide not to set blindness of the interventions to patients and doctors, because that setting blindness to patients and doctors will need placebo injections to some of the participants, which may bring unnecessary pain and tympanic membrane perforation risk to the patients. The specialists in test rooms and statistical analysts will be kept blinded during the trial until the statistical analyses are done.

### Trial management and quality control

A data monitoring committee (DMC) has been established to store, monitor, and check the authenticity, security, and integrity of the database. All members in the DMC are independent of the study sponsors and declared no competing interests. The DMC will periodically review the accumulated data and communicate the problems of its deliberations to the study team if necessary. The frequency of the interim analyses will be judged by the Chair of the DMC, based on the consultation with the TMC. We anticipate that there might be 2–3 interim analyses before the final analysis.

### Sample size and statistical methods

In our previous studies, we reported the poor indicator of the vestibular system lesion patterns in SSNHL and put forward that the incidence of vestibular dysfunction [30, 31]. However, we only found the existence of vestibular recovery in clinical case reports [16]. Due to lack of previous reported data on changes of vestibular function test results, this study sample size was calculated based on data from preliminary clinical practice in our hospital. Among patients who were diagnosed as ISSNHL and treated with oral prednisone, the recovery proportion of the vestibular function tests (measured by SOT, caloric test, or VEMPs) was 0.25, while the recovery proportion among those treated with intratympanic glucocorticoids was approximate 0.64. Using the program of G*Power 3.1 for Fisher’s exact test, we calculated a sample size of 30 per arm with 80% power at a two-tailed 5% level of significance [32]. To allow for 20% dropout, 36 participants per arm will be needed.

For the outcomes, categoric variables will be expressed as rates, while numerical variables as the mean ± SD. Baseline data will be compared between two groups with a chi-squared test for dichotomous samples and Student’s *t* test or Mann-Whitney *U* test for two independent samples where appropriate. For comparisons of recovery in 4 and 8 weeks from baseline, the recovery rates of vestibular function tests will be calculated by chi-squared tests, and logistic regression adjusts for potential confounders like age, initial PTA, the number of involved vestibular organs, MRI-IAC results, and other characteristics, while the numerical variables like UW of the caloric test, PTA, and scores in DHI, VAS-V, and VAS-T will be calculated by mixed-model with repeated measures analyses of variance (ANOVA), with group and time as fixed effects and subject as a random effect, controlling for the potential confounders. Between two intervention groups, the chi-squared test will be used to analyze the difference for dichotomous outcomes (e.g., recovery rates) and Student’s *t* test for two independent samples or Mann-Whitney *U* test where appropriate. A value of *p* < 0.05 of two-sided is considered statistically significant. We will calculate relative risk (RR) with corresponding 95% confidence intervals to compare dichotomous variables, and mean difference (MD) for continuous variables.

An ITT analysis and a per-protocol analysis will be both performed at each outcome. For the missing data in ITT analyses, if there is any, multiple imputation methods will be used. Up-to-date versions of SPSS (SPSS, Chicago, IL, USA) will be used to conduct analyses. A statistician from the Medical College of Fudan University will perform the analyses. Not until the statistician complete the analysis, will he be unblinded to the group allocations and the study hypotheses. All data sent to the analyst will be anonymized, and the study groups will be coded as groups A and B.

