**Methods/design:**

A randomized, outcome-assessor- and analyst-blinded, controlled, clinical trial (RCT) will be carried out. Seventy-two patients with ISSNHL complaining of vestibular dysfunction appearing as vertigo or imbalance will be recruited and randomized into either oral or intratympanic glucocorticoid therapy group with a 1:1 allocation ratio. The primary outcomes will be vestibular function outcomes assessed by sensory organization test, caloric test, video head impulse test, cervical vestibular evoked myogenic potential, and ocular vestibular evoked myogenic potential; the secondary outcomes include self-reported vestibular dysfunction symptoms; dizziness-related handicap, visual analogue scale for vertigo and tinnitus; and pure tone audiometry. Assessments of primary outcomes will be performed at baseline and at 4 and 8 weeks post-randomization, while assessments of secondary outcomes will be performed at baseline and 1, 2, 4, and 8 weeks post-randomization.

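### The dropout allowance is miscalculated: 36 per arm preserves the required 30 only up to 16.7% dropout, not the stated 20%; the effect on power is minor

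*Protocol article*

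**What the plan says.** All the figures are in the protocol article, mainly under Sample size and statistical methods.

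- Oral arm: "the recovery proportion of the vestibular function tests (measured by SOT, caloric test, or VEMPs) was 0.25".
- Intratympanic arm: "the recovery proportion among those treated with intratympanic glucocorticoids was approximate 0.64".
- Method: "Using the program of G*Power 3.1 for Fisher’s exact test".
- Size before dropout: "we calculated a sample size of 30 per arm with 80% power at a two-tailed 5% level of significance".
- Dropout allowance: "To allow for 20% dropout, 36 participants per arm will be needed".
- The Methods/design part of the Abstract carries the resulting total: "Seventy-two patients with ISSNHL complaining of vestibular dysfunction".

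The inflation formula is not written out. For the between-group analysis, the same section says "the chi-squared test will be used to analyze the difference for dichotomous outcomes" and does not mention a continuity correction.

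**The concern.** A dropout allowance should return the required number once the stated share of randomised patients has been lost, so the required number is divided by one minus the dropout proportion. The stated 36 is instead what one gets by multiplying by one plus that proportion, which always gives a smaller number. The article therefore implies that 30 per arm would remain after a 20% loss, and on its own figures they would not. What is at stake is whether the published statement can be reproduced and whether the stated 80% power survives the stated dropout.

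**Working it through.** **Inputs.** Recovery proportions 0.25 and 0.64, two-sided 5% level, Fisher's exact test, 80% power, 30 per arm before dropout, 20% dropout and 36 per arm, all from Sample size and statistical methods. The total of 72 is from the Abstract.

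**Step 1: reproduce the size before dropout.** Exact power is the sum of the two binomial probabilities over all outcome pairs for which Fisher's two-sided p is at most 0.05. It is 79.5% at 29 per arm and 81.9% at 30 per arm. The continuity-corrected normal formula also gives 30. The stated 30 therefore reproduces, and the fault lies only in the inflation step.

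**Step 2: the inflation.**
- n × (1 + d) = 30 × 1.2 = 36, which is the stated figure exactly.
- n / (1 − d) = 30 / 0.8 = 37.5, rounded up to 38 per arm, or 76 in total.
- Left after 20% loss from 36: 36 × 0.8 = 28.8 per arm, or 72 × 0.8 = 57.6 in total.
- Largest dropout that still leaves 30 of 36: 1 − 30/36 = 6/36 = 16.7%.
- Gap: 38 − 36 = 2 per arm, 4 in total.

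**Step 3: what this does to power.** A 20% loss from 72 is 14.4 patients, so 57 or 58 remain. Exact power by enumeration, with 0.25 and 0.64:

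| Patients left | Split | Fisher | Chi-squared, no continuity correction |
|---|---|---|---|
| 60 | 30/30 | 81.9% | 88.2% |
| 58 | 29/29 | 79.5% | 86.4% |
| 57 | 28/29 or 29/28 | 81.6% or 82.4% | 87.9% or 88.6% |
| 56 | 28/28 | 77.5% | 84.8% |

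The last row is not a 20% loss: 16/72 = 22.2%. Fisher power is higher with 57 patients than with 58 because the test is discrete, so power does not rise steadily with size.

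**The case against.** Four things can be said for leaving the sentence alone.

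1. **The gap is trivial.** It is two patients per arm, and the inputs are soft: the article takes the proportions from preliminary practice at its own hospital and calls the second one approximate. This stands as a limit on importance. It does not make 36, 30 and 20% consistent.

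2. **Dropouts are not simply removed.** The Primary outcomes section divides by all enrolled participants, and the plan is intention-to-treat with multiple imputation. The 28.8 per arm therefore describes patients with observed outcomes, not the size of the intention-to-treat set. This softens the effect, but imputation does not restore the information in unobserved outcomes. A per-protocol analysis is also planned, and the authors chose to make a dropout allowance.

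3. **Dropout might be counted as a share of completers.** Then 6/30 = 20% and 36 would be right. The article gives no such definition, and the plain reading is a share of those enrolled.

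4. **The planned test has power to spare.** This is correct for the chi-squared test without continuity correction.

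Two stronger readings are tempting and are not supported. A reader might infer that 72 patients fail to deliver 80% power at 20% dropout, or that power falls to 78%. The 77.5% figure belongs to 28/28, a 22.2% loss. At 20% loss, Fisher power is half a point below 80% for 29/29 and above 80% for 28/29. A reader might also infer that sizing on Fisher's test and analysing with a chi-squared test is an error. Without continuity correction, that choice is conservative, because the planned test has more power than the one used for sizing.

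**Conclusion.** The stated dropout allowance is wrong on the article's own figures: 36 per arm covers 16.7% dropout, and 20% would need 38 per arm. The point is minor. At a 20% loss the worst near-equal split (29/29) puts Fisher power 0.5 points below target, and the planned uncorrected chi-squared test remains at 86.4% or more. It is a correction to a published statement, not evidence of an underpowered trial.

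This rests on dropout meaning a share of those randomised, on losses spread about evenly across the arms, on the stated proportions of 0.25 and 0.64, and, for the chi-squared figures, on no continuity correction.

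**What to change.** Keep 72 patients and restate the sentence along these lines: 36 per arm allows for 16.7% dropout (30 evaluable per arm); with 20% dropout about 29 per arm remain, with Fisher power of about 80%. If the sponsor prefers to keep a full 20% allowance, the matching size is 38 per arm, 76 in total; the power figures above give no strong reason to recruit the extra four. No change to the choice of test is needed on this account. The cost is one sentence, with no additional patients and no change to the conduct of the trial.

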#### Secondary outcomes

Secondary outcomes include the change of subjective evaluations in vestibular, tinnitus, and hearing assessments:
Change of DHI and VAS-V, VAS-T scores: change of DHI and VAS-V scores from baseline at 1-, 2-, 4-, and 8-week follow-up.Change of PTA: change of average of PTA from baseline at 1-, 2-, 4-, and 8-week follow-up; in this study, we define a 10-dB PTA criterion as clinically significant difference based on a previous RCT [9].Safety: rates of study-related adverse events (AEs), such as short-term systemic use of glucocorticoids related SAEs and AEs, and intratympanic injection-related AEs.

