## Discussion

Vestibular dysfunction, commonly complained by patients as vertigo, dizziness, or lateropulsion, has been considered as a risk factor of profound hearing loss and poor prognosis [30–34]. Recently, researchers made their efforts to specify the lesion patterns of the vestibular system in ISSNHL and proposed that the utricle and superior vestibular pathway is the most vulnerable vestibular site in ISSNHL, followed by the lateral semicircular canal and superior vestibular pathway [30]. Severe vertigo and static imbalance markedly improve over a couple of days or weeks in most of patients, while some may suffer from long-term residual dizziness. Recovery of peripheral vestibular function and central vestibular compensation might be involved in this process. Vestibular function tests, such as SOT, caloric test, vHIT, and VEMP, are effective and objective methods to distinguish restoration of peripheral vestibular function and compensation of the central vestibular. It has been reported that in a few cases of SSNHL, function of otolith organs reflexed by VEMPs was absent at onset and recovered or improved after weeks to months [16]. These cases suggested the role of peripheral vestibular function restorations. When peripheral vestibular injury is failed to recover by itself, the central compensation will take place. However, due to few previous researches in this field, the roles and proportions of central compensation versus peripheral recovery remain uncertain.

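### The stated random-subject model gives every change from baseline one standard error, so week-8 intervals for the continuous outcomes are too narrow if correlation falls over time

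*Protocol article*

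**What the plan says.** Under *Sample size and statistical methods*, the protocol article sends "numerical variables like UW of the caloric test, PTA, and scores in DHI, VAS-V, and VAS-T" to a "mixed-model with repeated measures analyses of variance (ANOVA), with group and time as fixed effects and subject as a random effect", adjusted for potential confounders. Subject is the only within-patient term named. The section states neither a residual covariance nor a group-by-time term. For software it says "Up-to-date versions of SPSS (SPSS, Chicago, IL, USA) will be used to conduct analyses". The effect measure is "mean difference (MD) for continuous variables", and two-sample t or Mann-Whitney tests between the groups are planned as well.

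The visit schedules differ by outcome:

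- **DHI and VAS.** *Secondary outcomes* lists "change of DHI and VAS-V scores from baseline at 1-, 2-, 4-, and 8-week follow-up". With baseline that is five visits, at 0, 1, 2, 4 and 8 weeks. *Recruitments and randomization* gives VAS for tinnitus the same schedule.
- **UW.** It is part of the objective vestibular tests, which *Recruitments and randomization* places at 0, 4 and 8 weeks.
- **PTA.** The article disagrees with itself. *Secondary outcomes* has "change of average of PTA from baseline at 1-, 2-, 4-, and 8-week follow-up", while *Recruitments and randomization* says "the hearing outcome assessed by PTA will be performed at baseline and at 4 and 8 weeks after randomization".

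**The concern.** A random subject effect with independent, equal-variance residuals is compound symmetry. It gives every visit the same variance, and every pair of visits the same correlation, whether they are one week or eight weeks apart. Every change from baseline then receives the same pooled standard error.

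The trial's own setting makes that doubtful. Patients enter within 7 days of onset and treatment starts at once. The *Discussion* says "Severe vertigo and static imbalance markedly improve over a couple of days or weeks in most of patients", and adds that some patients keep long-term residual dizziness. DHI and VAS are bounded at zero, so their spread may also change as symptoms resolve.

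At stake is the stated precision of the trajectory. The Abstract makes the pattern and course of recovery an aim, and the secondary outcomes are defined as change from baseline at each visit. Those contrasts depend on the covariance assumption.

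**Working it through.** **The plan's own figures.** The plan states no SD, correlation or precision for this model, so there is nothing to reproduce for it. Its one calculated figure concerns the binary primary outcome (0.25 versus 0.64, Fisher's exact test). That reproduces: exact power is 79.5% at 29 and 81.9% at 30 per arm. The covariance model plays no part in it.

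**Inputs.** Visit times come from the protocol. The correlations are assumptions. Data are taken as complete and SDs as equal to 1 unless stated.

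**Formulas.** Let V be the true covariance matrix of the visits and N the number of patients.

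- Model variance of a change: 2 × (mean variance − mean covariance) / N, the same at every visit.
- True variance of the change to visit t: (V00 + Vtt − 2·V0t) / N.
- SE ratio r = √(model / true). N cancels. Coverage of a nominal 95% interval ≈ 2Φ(1.96 r) − 1.

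**Five visits, correlation falling linearly from a (1 week apart) to b (8 weeks apart).** The ten pairs of visits have lags 1, 2, 4, 8, 1, 3, 7, 2, 6 and 4, with mean 38/10 = 3.8. The mean correlation is therefore a − (a − b)(3.8 − 1)/7 = a − 0.4(a − b).

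| a to b | Mean corr. | Model 2(1 − mean) | True, week 8, 2(1 − b) | r, week 8 | Coverage, week 8 | r, week 1 |
|---|---|---|---|---|---|---|
| 0.7 to 0.5 | 0.62 | 0.76 | 1.00 | 0.872 | 91.2% | √(0.76/0.60) = 1.125 |
| 0.8 to 0.4 | 0.64 | 0.72 | 1.20 | 0.775 | 87.1% | √(0.72/0.40) = 1.342 |
| 0.8 to 0.3 | 0.60 | 0.80 | 1.40 | 0.756 | 86.2% | √(0.80/0.40) = 1.414 |

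Week-1 coverage is 97–99%. Simulation with 72 patients and 6,000–8,000 replicates per scenario gave week-8 coverage of 91.3%, 87.4% and 86.3%. Exponential decay of 0.7 to 0.95 per week gives r of 0.83 to 0.71 at week 8, or about 90% to 84% coverage.

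**Five visits, other structures.**

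- *Baseline-to-later 0.4, later-to-later 0.8.* Mean correlation is (4 × 0.4 + 6 × 0.8)/10 = 0.64, and r = √(0.72/1.20) = 0.775 at every visit (87.1%). Week 1 is now too narrow as well.
- *Constant correlation 0.5, SD falling through 1, 0.9, 0.8, 0.65, 0.5.* Mean variance is 0.6245 and mean covariance 0.2925, so the model value is 2 × 0.332 = 0.664. At week 1, r = √(0.664/0.91) = 0.85. At week 8, r = √(0.664/0.75) = 0.94.
- *Constant correlation 0.5, equal SD.* r = 1.00 at every visit.

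**UW, visits at 0, 4 and 8 weeks.** The lags are 4, 8 and 4, with mean 16/3. The mean correlation is a − (a − b)(16/3 − 1)/7 = a − 0.619(a − b).

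| a to b | Mean corr. | Model | True, week 8 | r, week 8 | Coverage |
|---|---|---|---|---|---|
| 0.7 to 0.5 | 0.576 | 0.848 | 1.00 | 0.92 | 93% |
| 0.8 to 0.4 | 0.552 | 0.895 | 1.20 | 0.86 | 91% |
| 0.8 to 0.3 | 0.490 | 1.019 | 1.40 | 0.85 | 91% |

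Under the 0.4/0.8 pattern, the mean is (0.4 + 0.4 + 0.8)/3 = 0.533 and r = √(0.933/1.20) = 0.88 (92%).

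**Between-arm tests.** Under the same decay scenarios with no treatment effect, the group main effect has type I error of 4.7–5.2%, and a two-sample t test on the week-8 change has 4.4–5.4%. Both hold their level.

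**The case against.** The strongest reply is that the article is silent on residual covariance, not wrong about it. A random subject effect can sit beside a structured residual matrix, and a condensed article may leave that structure to the analysis plan. This limits how firmly the point can be put: compound symmetry follows from the stated terms plus ordinary residuals, and the article does not say the residuals are ordinary. But the article does name its within-patient term. An analyst who fits what is written, and nothing more, gets one standard error for all changes.

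Three further objections stand and set the limits of the point.

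- **Direction.** A reader might infer that intervals are always too narrow at week 8 and too wide at week 1. The documents do not support that. They give no correlations, and the remark about rapid improvement describes average symptoms, not correlations. The week-1 error reverses if baseline is the poorly correlated visit, and both errors vanish under constant correlation and SD. UW has no week-1 value, and PTA may have none.
- **Treatment comparison.** A reader might infer inflated false positives for the week-8 difference between arms. If a group-by-time term were added, the same r would apply, and the error would be 1 − coverage: about 9%, 13% and 14% in the three five-visit scenarios. The stated model has no such term, and its group main effect keeps its level.
- **Reach.** The separate two-sample tests do not use the pooled standard error. The binary primary outcome and the sample size do not involve this model.

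**Conclusion.** The point holds in conditional form. As written, and with ordinary residuals, the model attaches one standard error to all changes from baseline. If correlation falls with time, or baseline correlates less with later visits than they do with each other, the nominal 95% interval for the baseline-to-week-8 change covers about 86–91% for DHI and VAS and about 91–93% for UW. PTA falls in the first or second range according to which of its two schedules is followed.

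These figures rest on assumed correlations, equal SDs and complete data. UW will not be complete, because *Time points* repeats only the tests that were previously abnormal. Early-visit intervals can err in either direction.

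The consequence is moderate. The exposed inference is the time contrasts of the continuous outcomes, that is, how precisely recovery over 8 weeks is described. The written plan's tests of one treatment against the other are not affected. The change is worth making because the better method is standard and cheap.

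**What to change.** In *Sample size and statistical methods*, replace the random subject effect by an unstructured within-patient covariance across visits, with Satterthwaite or Kenward-Roger degrees of freedom. Name one fall-back for non-convergence, for example heterogeneous Toeplitz. If a group-by-time term is added to estimate week-specific differences between arms, the same covariance should apply to it. The PTA schedule must be reconciled so that the number of visits in its model is known.

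The cost is one sentence. With five visits there are 5 × 6/2 = 15 covariance parameters, and with three visits 3 × 4/2 = 6, estimated from 72 patients. Intervals will be slightly wider at some visits. If the correlation is in fact constant, little precision is lost.
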